## Abstract

**Background:**

In the USA, stillbirth (in utero fetal death ≥20 weeks gestation) is a major public health issue. Women who experience stillbirth, compared to women with live birth, have a nearly sevenfold increased risk of a positive screen for post-traumatic stress disorder (PTSD) and a fourfold increased risk of depressive symptoms. Because the majority of women who have experienced the death of their baby become pregnant within 12–18 months and the lack of intervention studies conducted within this population, novel approaches targeting physical and mental health, specific to the needs of this population, are critical. Evidence suggests that yoga is efficacious, safe, acceptable, and cost-effective for improving mental health in a variety of populations, including pregnant and postpartum women. To date, there are no known studies examining online-streaming yoga as a strategy to help mothers cope with PTSD symptoms after stillbirth.

**Methods:**

The present study is a two-phase randomized controlled trial. *Phase 1* will involve (1) an iterative design process to develop the online yoga prescription for phase 2 and (2) qualitative interviews to identify cultural barriers to recruitment in non-Caucasian women (i.e., predominately Hispanic and/or African American) who have experienced stillbirth (*N* = 5). *Phase 2* is a three-group randomized feasibility trial with assessments at baseline, and at 12 and 20 weeks post-intervention. Ninety women who have experienced a stillbirth within 6 weeks to 24 months will be randomized into one of the following three arms for 12 weeks: (1) intervention low dose (LD) = 60 min/week online-streaming yoga (*n* = 30), (2) intervention moderate dose (MD) = 150 min/week online-streaming yoga (*n* = 30), or (3) stretch and tone control (STC) group = 60 min/week of stretching/toning exercises (*n* = 30).

**Discussion:**

This study will explore the feasibility and acceptability of a 12-week, home-based, online-streamed yoga intervention, with varying doses among mothers after a stillbirth. If feasible, the findings from this study will inform a full-scale trial to determine the effectiveness of home-based online-streamed yoga to improve PTSD. Long-term, health care providers could use online yoga as a non-pharmaceutical, inexpensive resource for stillbirth aftercare.

**Trial registration:**

NCT02925481

## Background

In the USA, the death of a baby to stillbirth (in utero fetal death ≥20 weeks gestation) is a major public health issue. Each year more than 26,000 babies are stillborn, and in many cases, even after a postmortem evaluation, the cause is unknown [1]. Many mothers suppress their grief and feel stigmatized, socially isolated, and their baby’s lives devalued by society [2]. These experiences seem to worsen trauma reactions, such as despair, thoughts of suicide, anxiety, guilt, shame, and anger [3–5]. Symptoms can last up to 18 years [6–8] and are likely to re-occur in subsequent pregnancies [9, 10]. In an effort to destigmatize stillbirth, *The Lancet* has published two issues dedicated entirely to stillbirth in 2011 and 2016 [11, 12].

### Psychological health

Women who experience stillbirth, compared to women with live birth, have a nearly sevenfold increased risk of a positive screen for post-traumatic stress disorder (PTSD), a fourfold increased risk of depressive symptoms, twice the risk of a positive screen for generalized anxiety disorder [13, 14]. Symptoms of PTSD and its associated comorbidities (e.g., anxiety and depression) may contribute to diminished self-compassion (i.e., poor self care), emotional dysregulation, and compromised sleep quality, all of which have been associated with declining physiological well-being, weight retention/gain, increased chronic disease risk (e.g., heart disease, diabetes), premature mortality, poor quality of life, and cognitive delays in subsequent children [15–17]. Because the majority of women who have experienced the death of their baby become pregnant within 12–18 months [18], novel approaches targeting physical and mental health, specific to the needs of this population, are critical.

### Interventions

A recent Cochrane review [19] demonstrates the need for clinical trials to assess interventions to support women after the loss of a baby to stillbirth. A recent systematic review [20] evaluated intervention studies in bereaved mothers after stillbirth and identified only two [one small RCT and one feasibility study (outside of US)] from 1980 to 2015. One RCT evaluated a support group in women after a stillbirth compared to a no-treatment concurrent control group. The authors concluded that grief counseling may reduce grief symptomology after a stillbirth. This is particularly salient in mothers with poor social support [21]. The other explored the feasibility, acceptance, and cultural fit of a brief mindfulness-based intervention to reduce perinatal grief and other mental health indices (i.e., depression, coping) among Indian mothers [22]. There were significant improvements in anxiety, depression, coping, life satisfaction, social provisions, and mindfulness as a result of the intervention.

Given the lack of intervention studies conducted within this population, more research with appropriate control groups are needed to inform evidence-based care.

### Rationale for study

The most common treatments for PTSD are exposure therapy [23], eye movement desensitization and reprocessing (EMDR) [24], referral to support groups/interpersonal counseling [25, 26], and/or psychiatric medication or other medications to treat physical symptoms [27]. Although these strategies demonstrate some effectiveness in the general population with PTSD, they are unlikely to be fully effective for bereaved mothers for a variety of reasons. First, bereaved mothers’ engagement in treatment (e.g., initiation of therapy, support groups) is uncommon (<25%) [13]. Second, because bereaved mothers may be trying to conceive again, or have already conceived, they are often reluctant to take psychiatric medication, preferring non-pharmacologic alternatives [1]. In addition, medication cannot address the psychosocial aspects of grief and the accompanying emotional distress [28]. Third, though support groups for bereaved parents may provide a familiar and safe environment to connect with others who have had similar experiences [29, 30], these groups often have little to no emphasis on adaptive coping strategies for PTSD symptoms (e.g., hypervigilance, intrusion, avoidance) and the underlying emotional etiology [19, 31]. Fourth, bereaved mothers report unique barriers to participation in activities outside the home, such as encountering other babies in public, and many express strong interest in home-based treatments [32]. Finally, women may not have access to specialized treatment (e.g., exposure therapy, support groups) based on where they live, insurance coverage, or access to specialized clinicians, resulting in limited options for treatment [30, 33, 34]. It is crucial for science to develop novel approaches to inter-conception care amenable to the needs of these mothers.

Yoga may be an ideal treatment for addressing the unique PTSD symptoms of bereaved mothers after the death of a baby. Several studies have demonstrated that yoga is efficacious, safe, acceptable, and cost-effective for improving mental health in a variety of populations, including pregnant and postpartum women [35–41]. Yoga has also been used as a means to cope with PTSD symptoms after traumatic events (e.g., interpersonal violence, war, natural disasters) [42–45]. To date, there are no known studies examining yoga as a strategy to help bereaved mothers cope with PTSD symptoms after stillbirth.

This manuscript will describe a study protocol for a three-group randomized feasibility trial in US-based mothers and follows the reporting guidelines outlined by the SPIRIT checklist [46]. This study has the following objectives:Examine the feasibility and acceptability of a 12-week, home-based, online-streamed yoga intervention, with varying doses (low = 60 min/week; moderate = 150 min/week) among bereaved mothers who have experienced the death of a baby to stillbirth. Feasibility is defined as acceptability, demand, and practicality (see the “Outcome measures” section for operational definitions).Adapt an already established, evidence-based control group [47–50] and determine its acceptability for a future randomized controlled trial. Adaptation is defined as age- and population-specific. Acceptability is defined as adherence and satisfaction.Ascertain the preliminary effects of the intervention on reducing PTSD symptoms below the clinical threshold.Explore potential mechanisms (i.e., self-compassion, emotional regulation, sleep disturbance) by which yoga may reduce PTSD symptoms in bereaved versus non-bereaved mothers. We will also determine intervention effects on co-morbid conditions such as anxiety and depression.

## Methods/design

### Study design

The study will occur within two phases—one for the formative work to inform the intervention and another to implement the intervention (see Fig. 1 for a flow chart of study phases).

**Fig. 1 Fig1:**
[figure not shown]
Study flow chart: the *left side* of the diagram illustrates the flow of the study for phase 1, and the *right side* illustrates the phase 2

#### Phase 1

Part A. Iterative design: We will develop the yoga prescription using an iterative design process with the following steps:Identify 30 videos from the existing UDAYA (an online-streaming commercial yoga website; https://udaya.com) library.Gather a panel of women whose babies were stillborn (*n* = 5) and a panel of women who are regular yoga practitioners and have not experienced a baby’s death (*n* = 5) to review (i.e., watch or engage) yoga videos selected from step one above.Develop (produced by Udaya.com) up to 12, 30-min yoga videos specifically for the grieving mothers.

Part B. Interviews to identify cultural barriers to recruitment: We will recruit five non-Caucasian (predominately Hispanic and/or African American) women who have experienced stillbirth to participate in a 15–20 min phone interview. These interviews will guide the recruitment process for phase 2, and additional recruitment materials will be developed to ensure adequate enrollment of non-Caucasian women in the study. The interview questions will consist of questions related to:Perceptions/opinions about yoga related to physical and mental health.Strategies to ensure adequate enrollment and retention of non-Caucasian women to participate in a yoga intervention.

#### Phase 2

Phase 2 is a three-group randomized feasibility trial with assessments at baseline and at 12 and 20 weeks from baseline. After completion of the consent process and the baseline assessment, 90 women will be randomized into one of the following three arms for 12 weeks: (1) intervention low dose (LD) = 60 min/week yoga (*n* = 30), (2) intervention moderate dose (MD) = 150 min/week yoga (*n* = 30), or (3) stretch and tone control (STC) group = 60 min/week of stretching/toning exercises (*n* = 30).

### Eligibility criteria

Inclusion and exclusion criteria for phase 1 (iterative design and interviews) are described in Table 1, and those for phase 2 are described in Table 2.

**Table 1 Tab1:** Phase 1 eligibility criteria

Inclusion
Iterative design
• Able to read/understand/speak English
• Women who experienced stillbirth within past 6 weeks to 24 months OR
• Women who have not experienced stillbirth but have given at least one live birth who regularly practice yoga (participate in yoga >60 min/week)
Interviews
• Able to read/understand/speak English
• Racial/ethnic minority women
• Women who experienced stillbirth within past 6 weeks to 24 months
• Not regularly practicing yoga (participating in yoga <60 min/week)
• Underactive (≤120 min/week moderate-intensity physical activity)
Exclusion
Iterative design
• Women who have experienced stillbirth that regularly practice yoga (i.e., ≥60 min/week)
• Pregnant women
• Unstable psychiatric condition (psychosis; suicidal ideation with plan)
Interviews
• Caucasian women
• Unstable psychiatric condition (psychosis; suicidal ideation with plan)

**Table 2 Tab2:** Phase 2 eligibility criteria

Inclusion
• Women who experienced stillbirth within past 6 weeks to 24 months
• Clinical levels posttraumatic stress symptoms (score of ≥33 on IES)
• ≥18 years of age
• Residing in the USA
• Able to read/understand/speak English
• Underactive (≤120 min/week moderate-intensity physical activity)
• Willing to be randomized
• Regular internet access via mobile phone, desktop/laptop computer, tablet, and etc.
• Answer “no” to all items on the PAR-Q (can participate safely)
Exclusion
• Unstable psychiatric condition (psychosis; suicidal ideation with plan)
• Pregnant at time of enrollment^a^
• Practicing yoga at least 60 min/week
• Unwilling to be randomized to a group
• Score of 20–27 of PHQ-9 (severe depression score)
• At risk for suicide based on follow-up phone assessment by [name] after positive screen (PHQ-9 score of 1, 2, or 3)

^a^Pregnant women will not be eligible for initial recruitment into the study. Women who become pregnant during the study will complete a PARmed-X for Pregnancy with their physician to identify any contraindications to yoga and will be able to continue participation

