##### Iterative design

Women (*N* = 10) will be asked to come to the Healthy Lifestyles Research Lab at a *University in the Southwestern United States* for nine sessions (i.e., 20–60 min)*.* Thirty online yoga videos from Udaya’s library, preselected by a yoga therapist and the principal investigator, will be randomly assigned (using a random number table) to participants. Each participant will be randomly assigned nine different online yoga videos so that each video is reviewed at least three times. Selection criteria for the 30 online yoga videos include the following: (1) have been used in our previous beta-testing [51] *and were* positively reviewed by mothers bereaved by stillbirth, (2) videos that the research team believes will cultivate emotional regulation and self-compassion (evidence-based proposed mediators from a general population with PTSD), (3) classes that are slower moving (i.e., beginner-based) with detailed instruction and alignment cues (i.e., safe and proper form), and (4) classes that are safe for women up to 20 weeks gestation in case a woman becomes pregnant during the intervention. Each woman will be asked to watch/engage in the yoga video by herself in an observation room. Participants will not be able to review more than one video per day to limit influence from another video. Before and after engaging in the yoga videos, women will be asked two investigator-developed questions related to the potential mechanisms by which yoga may reduce PTSD symptoms, including self-compassion [How much self-compassion do you feel (i.e., self-kindness, understanding toward yourself and your grief, common humanity, mindfulness) right now?] and emotional regulation [How much do you feel that you are able to be with your emotions (i.e., consciously stay with your emotions or mood) right now?]. Questions will be answered on a five-point Likert scale. Mean scores will be taken for each video and entered into an Excel document. Those videos that elicit the *highest* self-compassion and/or emotional regulation will *be used for phase 2*.

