### Study enrollment

Interested participants will complete an eligibility screener (approximately 5–10 min) on Qualtrics. The screener will only allow one entry per IP address to prevent “ballot box stuffing.” Additionally, there will be a final question on the screener asking the participant to confirm all responses. Upon submitting the screener, participants will no longer have access to the screener. Research team members will follow an Institutional Review Board (IRB)-approved script to respond to interested participants who phone or email and refer them to the eligibility screener (participants provide consent electronically to complete the eligibility screener). All ineligible participants will be notified by phone and/or email and offered a discounted Udaya.com membership ($9/mo., compared to $12/mo.)

#### Phase 1

Iterative design: Eligible participants (see Table 1 for eligibility criteria) will receive an email requesting times to schedule their first visit to the lab on the university campus. During the participant’s first visit, they will complete an informed consent document.

Interviews: Eligible participants will receive an email requesting times to schedule their 15–20-min phone interview. Following, participants will be sent a Qualtrics link asking them to electronically sign an informed consent document before their scheduled interview.

#### Phase 2

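### Table 1 has no PAR-Q criterion for phase 1 women who do the yoga videos, although Table 2 requires one in phase 2; secondarily, no balance by panel is stated for the video assignment

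*Protocol article*

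**What the plan says.** Under Eligibility criteria, the article states that "Inclusion and exclusion criteria for phase 1 (iterative design and interviews) are described in Table 1". For the iterative design, Table 1 asks for English and either a stillbirth 6 weeks to 24 months ago or, for the comparison panel, a live birth, no stillbirth and regular yoga. It excludes pregnancy, an unstable psychiatric condition and "Women who have experienced stillbirth that regularly practice yoga (i.e., ≥60 min/week"). No physical-readiness questionnaire is listed. Table 2, for phase 2, requires the answer no "to all items on the PAR-Q (can participate safely").

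Under Study enrollment, Phase 1, Table 1 is the working list: "Eligible participants (see Table 1 for eligibility criteria) will receive an email requesting times to schedule their first visit to the lab". Informed consent is the only step named for that visit.

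Under Interventions, Phase 1, Iterative design, ten women attend nine sessions of 20 to 60 minutes: "Each woman will be asked to watch/engage in the yoga video by herself in an observation room". Thirty videos are allocated with a random number table: "Each participant will be randomly assigned nine different online yoga videos so that each video is reviewed at least three times". Study design, Phase 1, Part A describes two panels of five. The first is introduced as "Gather a panel of women whose babies were stillborn"; the second consists of regular yoga practitioners who have not had a baby die. No rule linking the allocation to panel is given.

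**The concern.** The sponsor has set its own test of whether a woman can safely do online yoga, and it makes that test a condition of entry to phase 2. Phase 1 asks women from the same bereaved population, again not regular practitioners, to watch or do yoga videos, and its published criteria leave the test out. If staff follow Table 1, a woman whom the sponsor would turn away from phase 2 on physical grounds can do the phase 1 sessions.

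The secondary issue is who rates the videos. They are being chosen for bereaved mothers, and one of the two rating questions refers to the respondent's own grief, yet half of the raters have not had this loss. A draw that ignores panel can leave some videos with no rating from a bereaved woman in this phase.

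**Working it through.** **Physical screen.** This part is a comparison of texts, with one piece of arithmetic.

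- Table 1, iterative design: no PAR-Q or equivalent; pregnancy is the only physical exclusion.
- Table 2, phase 2: no to every PAR-Q item is an inclusion criterion.
- Study enrollment, Phase 1: eligibility under Table 1 leads directly to scheduling the lab visit.
- No other section of the article mentions a physical screen for phase 1.
- Possible exposure per woman if she does every session: 9 × 20 = 180 minutes to 9 × 60 = 540 minutes. If she only watches, it is zero.

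**Panel balance.** Inputs: 10 women (5 bereaved, 5 practitioners), 9 different videos each, 30 videos, at least 3 reviews per video.

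1. The plan's own figure: 10 × 9 = 90 reviews, and 90 / 30 = 3 per video. The stated minimum is reproduced. With no slack, it can be met only by exactly three reviews for every video.
2. Assumption: the draw is made over all ten women without regard to panel. The three reviewers of a given video are then a random three out of ten.
   - No bereaved reviewer: C(5,3) / C(10,3) = 10 / 120 = 0.083. Expected videos: 30 × 0.083 = 2.5.
   - Exactly one bereaved reviewer: 5 × C(5,2) / C(10,3) = 50 / 120 = 0.417. Expected videos: 30 × 0.417 = 12.5.
3. Chance that at least one of the 30 videos has no bereaved reviewer:
   - Treating videos as independent: 1 − (1 − 0.0833)^30 = 0.926.
   - Simulating whole designs that hold 9 videos per woman and 3 reviews per video: 0.96, with a mean of 2.5 such videos and a 95% range of 0 to 5.
4. Draw within panel: each panel supplies 5 × 9 = 45 reviews, or 1.5 per video. The most even split is 15 videos with two bereaved reviewers and one practitioner, and 15 with one and two (15 × 2 + 15 × 1 = 45 for each panel). No video is then rated by one panel only.
5. Feasibility of step 4: number the videos 1 to 30 in random order and the bereaved women 0 to 4.
   - Woman k takes the six videos whose number leaves remainder k on division by 5.
   - She also takes the three videos among 1 to 15 that leave the next remainder (0 follows 4).
   - That is 6 + 3 = 9 different videos each; videos 1 to 15 get two bereaved reviewers and videos 16 to 30 get one.
   - The practitioners follow the same rule with 16 to 30 as the doubled half. Every video then has three reviews.

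**The case against.** The strongest reply is that this is a condensed article. Table 1 looks abridged (it also omits the age limit that Table 2 gives), the items of the online eligibility screener are not shown, and the article mentions approved protocols and a manual of procedures. A PAR-Q may have been asked. A reader might infer that phase 1 had no physical screening at all; the article does not establish that. What stands against the reply is that eligibility is published here as an itemised list and used as such for scheduling, so the list as published gives no ground for limiting a woman on the PAR-Q.

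A lighter screen in phase 1 can also be defended. The prescribed dose in phase 2 is 12 × 60 = 720 or 12 × 150 = 1,800 minutes at home. Phase 1 is at most 540 minutes, no more than one video a day, in an observation room, with watching allowed. The videos are beginner-paced, preselected by a yoga therapist, cued for proper form and chosen to be safe up to 20 weeks of gestation, and half of the women practise regularly. This lowers the risk and is part of why the point is minor. It does not replace an individual screen: phase 2 videos must also be suitable up to 20 weeks of gestation, and the sponsor still requires the PAR-Q there.

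A reader might also treat all 5 × 9 = 45 sessions of the bereaved panel as sessions at risk. That would be wrong: the count says nothing about how many women would fail a PAR-Q or would take part physically.

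On panel balance, the text does not say that the draw ignores panel, and a within-panel draw is compatible with it. The selection criteria require that the 30 videos had already been well received by bereaved mothers in earlier testing, so none lacks bereaved input altogether. A reader might go further and conclude that scores are pooled across panels, or that a video badly received by bereaved women would be chosen. The article gives a mean score per video but does not set out how panels enter it, so neither conclusion is supported. Part A also plans "up to 12, 30-min yoga videos specifically for the grieving mothers", so the reviewed library videos are not the only material for phase 2.

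**Conclusion.** The main point holds as a minor improvement. As published, the criteria let iterative-design women do up to nine yoga sessions without the physical-safety screen that the sponsor requires in phase 2. It is a gap between two lists, not a contradiction or evidence of harm. The number of women who would fail the screen is unknown and may be zero.

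The secondary point is conditional. If the assignment is unstratified, about 2.5 of 30 videos are expected to have no bereaved reviewer in this phase, and at least one such video is very likely (93% to 96%). If the draw was made within panel, the point falls away.

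Neither point affects phase 2 randomisation, outcomes or any sample-size figure. Confidence is medium, because a fuller protocol could contain both the screen and the stratification.

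**What to change.** 1. Add the Table 2 PAR-Q criterion to the iterative-design inclusion list in Table 1 for women who will do the videos, and state that a woman who does not meet it may only watch. Cost: one line and a self-report form already used in phase 2. Downside: a few volunteers are limited to watching.
2. In the Iterative design section, state that videos are randomly assigned within panel, so that each has one or two bereaved reviewers and three reviews in total. Cost: one phrase, with no extra women or sessions. An equal split within a video is impossible because three is odd, so 15 videos will still have a single bereaved reviewer.
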